# Acupuncture for prostatectomy incontinence: study protocol for a multicenter single-blind randomized parallel controlled trial

**DOI:** 10.1186/s13063-021-05805-5

**Published:** 2022-01-04

**Keywords:** Acupuncture, Post-prostatectomy incontinence, Efficacy, Randomized control trial, Study protocol

## Abstract

**Background:**

Urinary incontinence is a common complication post radical prostatectomy. Acupuncture is considered an effective treatment for post-prostatectomy incontinence (PPI), but the evidence is still limited. We propose to evaluate the effectiveness of acupuncture in a rigorously conducted trial.

**Methods:**

Twenty hospitals will recruit 340 participants with urinary incontinence after radical prostatectomy in China from April 2021 to April 2022. Participants will be randomly allocated to acupuncture or sham acupuncture with a 1:1 ratio using computerized simple random sampling. The study plan consists of 1-week baseline, 6-week treatment, and 18-week follow-up. Eighteen 30-min sessions of acupuncture or sham acupuncture treatment will be provided between weeks 1 and 6. The primary outcome is the change in the International Consultation on Incontinence Questionnaire-Urinary Incontinence Short Form (ICIQ-UI-SF) score at the week 6 from the baseline. Secondary outcomes include the change in volume of urine leakage at weeks 4 and 6 from a baseline measured using the 1-h pad test; 72-h incontinence episode frequency based on a 72-h voiding diary; change in the Expanded prostate cancer Index Composite scale (EPIC-26); change in the Self-Rating Anxiety Scale; weekly consumption of pads; and the severity of urinary incontinence based on a 72-h bladder diary and self-assessment of the therapeutic effect. The safety of acupuncture will also be assessed.

**Discussion:**

This trial will help to identify whether acupuncture is effective for PPI, and, if so, whether it exerts a therapeutic rather than a placebo effect.

**Trial Registration:**

www.Chictr.org.cnChiCTR2100042500. Retrospectively registered on 22 January 2021.

**Supplementary Information:**

The online version contains supplementary material available at 10.1186/s13063-021-05805-5.

## Background

Prostate cancer is one of the most common malignant tumors of the male genitourinary system and radical prostatectomy is the first-line treatment for localized prostate cancer [1]. Post-prostatectomy incontinence (PPI) is a known complication with an incidence rate ranging from 4% to 31% [2], which has a significant impact on men’s quality of life (QoL) [3, 4]. The complication may generate feelings of low self-esteem, anxiety, and depression. The patients’ shame and discomfort arise from the inability to control the bladder. Patients who do not wish to wear a diaper daily, but always carry it for safety in their bag when leaving home [5]. The present study revealed that the postoperative period of 2 to 6 months had a severe impact on their QoL [6].

The treatments for PPI are mainly divided into two types. Conservative treatment includes bladder or pelvic floor muscle training [7, 8], biofeedback [9, 10], and drug therapy [11, 12]. Surgical intervention mainly includes artificial urethral sphincter implantation [13], urethral suspension [14, 15], or injection therapy [16]. All these treatments may benefit patients; Although, it cannot be denied that the selective serotonin reuptake inhibitor drugs such as duloxetine, which is often accompanied by symptoms of insomnia, nausea, loss of appetite, irritability, and other side effects [11, 17]. Further, surgical interventions are traumatic forms of treatment and are also costly [18]. Pelvic floor muscle training is the most used conservative treatment for urinary incontinence, but for elderly male patients with prostate cancer, whether functional training is carried out correctly is difficult to evaluate and assess, and it is challenging to implement.

Acupuncture is a typical treatment modality of traditional Chinese medicine (TCM) [19, 20]. With few adverse effects, TCM may be used as an alternative treatment approach for patients. Many research centers, mostly in China, have conducted clinical trials to evaluate the safety and effectiveness of acupuncture in managing PPI. Zhishun Liu and Yan Liu et al. [21] conducted a multicenter, randomized clinical trial and revealed that women with stress urinary incontinence can benefit from electroacupuncture involving the lumbosacral region, compared with sham electroacupuncture, resulting in less urine leakage after 6 weeks; the effects persisted 24 weeks after treatment and the incidence of adverse events was low. Huan Chen and Yu Liu et al. [22] in a meta-analysis of seven studies including 830 men with PPI showed that acupuncture can significantly improve the score of the International Consultation on Incontinence Questionnaire-Urinary Incontinence Short Form for men with urgent urinary incontinence (UUI) when compared with medicine, and no adverse event was reported in the studies. Therefore, acupuncture could be considered as an effective treatment for urinary incontinence.

However, the quality of evidence has been low and inconclusive. Therefore, we plan to perform a multicenter randomized controlled trial (RCT) to investigate the efficacy and safety of acupuncture in the treatment of PPI in patients with prostate cancer.

## Methods

### Study design

This study is a multicenter, single-blind, randomized parallel controlled prospective clinical trial with the objective of estimating the efficacy and safety of acupuncture on PPI by comparing a verum acupuncture group with a sham acupuncture group. Participants considered suitable for the study will be randomly allocated into the intervention group (verum acupuncture) or the control group (sham acupuncture) in a 1:1 ratio. This is a clinical trial of superiority.

### Study participants

#### Population

A target sample of 340 participants will be recruited from 20 hospitals across China: Tianjin Medical University General Hospital; The Second Hospital of Tianjin Medical University; Tianjin Medical University Cancer Hospital; Tianjin First Central Hospital; Tianjin Third Central Hospital; Peking University Third Hospital; Dongzhimen Hospital affiliated to Beijing University of Chinese Medicine; West China Hospital of Sichuan University; Benxi Central Hospital; First Affiliated Hospital of Dalian Medical University; The Second Hospital of Dalian Medical University; The First Affiliated Hospital of Kunming Medical University; Qinghai University Affiliated Hospital; Jiangsu Province People’s Hospital; First Hospital of Shanxi Medical University; Shandong Province Hospital; The Fifth People’s Hospital of Jinan; Inner Mongolia People’s Hospital; The Second Hospital of Anhui Medical University; and Guizhou Province People’s Hospital. Informed consent will be obtained from all participants before randomization.

#### Baseline assessment

A baseline registration will be performed before treatment. Participants will provide a review of basic information, malignancy history including operation history, pathology, and QoL assessment including urinary incontinence. A safety evaluation will also be performed.

#### Recruitment

We will recruit participants who are attending the 20 abovementioned hospitals in this trial. We will use WeChat to publish recruitment information, and use the “recruiters” applet to recruit and retrieve information for patients. Before recruiting patients, the researchers of each sub-center will explain the research protocol to potential trial participants and ask the patients sign the informed consent. The informed consent is in duplicate, one is owned by the participant or authorised surrogate and the other one is owned by the researcher. Finally, all the informed consent forms of each sub-center will be submitted to the project leader.

#### Inclusion criteria

Patients who meet all the following requirements will be allowed to enroll:
Patients who have received radical prostatectomy with a definite pathological diagnosis of prostate cancer:Patients with urinary incontinence symptoms, which refer to the meaning of urinary incontinence by the International Continuity Society or evaluated by the urologists as experiencing urinary incontinence resulting from radical prostatectomy [23];Karnofsky Score ≥ 60 or Eastern Cooperative Oncology Group (ECOG) Score 0–2; andWilling to participate in the study and sign the consent forms.

#### Exclusion criteria

Patients who meet all the following criteria will be excluded:
Urgency urinary incontinence caused by detrusor overactivity and bladder spasm, and urinary incontinence caused by neurogenic urethral dysfunction;Urinary incontinence treated by cystostomy, urethral sphincter reconstruction, or urethral suspension;Currently receiving less than 6 months treatment similar to acupuncture (such as electroacupuncture, warm moxibustion, and warm acupuncture);Judged by urologists as complete urinary incontinence;Urinary tract infection (except asymptomatic bacteriuria);History of severe arrhythmia, severe cardiac insufficiency, acute myocarditis, constrictive pericarditis, pericardial tamponade, severe valvular disease, heart failure, or other serious heart diseases;History of severe liver injury or potentially severe liver disease (ALT or AST > 10 times normal);History of severe renal impairment (estimated GFR < 25 mL/min/1.73 m^2^);Known to coagulation dysfunction (with typical clinical diagnosis or clear laboratory test results);Patients with mental illness or cognitive impairment, or severe depression;Patients who are not suitable to participate in this study or who are likely to withdraw from the study based on the judgment of the researchers; andPatients participating in other clinical trials.

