### Permitted and prohibited concomitant treatments

Both groups can receive conventional treatment for prostate cancer (such as endocrine therapy) and/or pelvic floor muscle training, which differ from acupuncture principles. Researchers need to keep a detailed record. Treatments like the principles of acupuncture are not allowed.

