### Safety assessment

To exclude any related serious diseases, patients will be asked to undergo necessary inspection before randomization, including vital signs, blood routine, urine routine, biochemical items, ECG. These tests will be performed at the week 6 of the study to evaluate the safety of this trial. If any AEs occur during the trial, patients will be treated as soon as possible.

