### Statistical methods

#### Sample size calculation

By enrolling approximately 340 (170 in each group) participants, the study will provide 90% power to detect a between-group difference of 2.5 in reduction of ICI-Q-SF score from baseline using a 2-sided alpha level of 0.05, and assuming a common standard deviation of 6.3 and a dropout rate of 20%. A difference of 2.5 points in the ICI-Q-SF score was selected for sample size calculations, which is indicative of a clinically significant change [24–26].

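### The exclusion lead-in says 'all' where 'any' must be meant, and the acupuncture-like-treatment item is ambiguous and does not fit the concomitant-treatment ban

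*Protocol article*

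**What the plan says.** The Inclusion criteria section begins "Patients who meet all the following requirements will be allowed to enroll", which is the right connective for inclusion. The Exclusion criteria section uses the same construction: "Patients who meet all the following criteria will be excluded". Twelve items follow:

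1. urgency or neurogenic incontinence
2. incontinence already managed by certain procedures
3. treatment resembling acupuncture
4. complete incontinence
5. urinary tract infection
6. serious heart disease
7. severe liver disease
8. severe renal impairment
9. coagulation dysfunction
10. mental illness, cognitive impairment or severe depression
11. the researcher's judgement that the man is unsuitable or likely to withdraw
12. participation in another trial

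Item 3 is worded "Currently receiving less than 6 months treatment similar to acupuncture", with electroacupuncture, warm moxibustion and warm acupuncture as examples.

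Two other sections bear on this. Permitted and prohibited concomitant treatments states "Treatments like the principles of acupuncture are not allowed". Safety assessment states "To exclude any related serious diseases, patients will be asked to undergo necessary inspection before randomization". Nowhere does the article restate the exclusion rule with 'any'.

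**The concern.** The lead-in governs who may be randomized. With 'all', a man with coagulation dysfunction alone, or urgency incontinence alone, is not excluded by the text, although the first matters for safety in a needling trial and the second for the population the trial is meant to study.

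Item 3 is a separate problem. Its wording turns on current treatment of short duration. It says nothing about a man who has been receiving such treatment for 6 months or longer, or about one who stopped shortly before screening. A reader can guess that 'all' means 'any', but cannot safely guess what the 6 months refers to. Twenty hospitals recruit (Population section) and could apply the item differently.

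**Working it through.** **The connective.** The list contains 12 items. Suppose, purely for illustration, that each item has the same prevalence p and that the items are independent; the article gives no prevalences. The share of men excluded is then:

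- under 'all': p^12
- under 'any': 1 − (1 − p)^12

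| Assumed p | Excluded under 'all' | Excluded under 'any' |
|---|---|---|
| 2% | 4 × 10⁻²¹ | 22% |
| 10% | 1 × 10⁻¹² | 72% |
| 20% | 4 × 10⁻⁹ | 93% |

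Independence is a simplification. Whatever the dependence, the share under 'all' cannot exceed the prevalence of the rarest item. The 'any' column shows only how far apart the two rules lie and is no forecast of screen failures.

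**What was intended.** Safety assessment has tests done before randomization in order to exclude serious disease, which has a purpose only if one such disease is enough. Item 11, the researcher's judgement of unsuitability, makes sense only as a stand-alone ground. Under Randomization and blinding, urologists screen patients before logging in to the randomization system. The shared sentence pattern suggests that 'all' was carried over from the inclusion lead-in.

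**Item 3, with the lead-in already corrected to 'any'.** Three meanings are possible:

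| Man at screening | Duration limit (as worded) | Ban on any current use | 6-month look-back |
|---|---|---|---|
| Currently treated, under 6 months | excluded | excluded | excluded |
| Currently treated, 6 months or more | eligible | excluded | excluded |
| Stopped within the last 6 months | eligible | eligible | excluded |

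The meanings disagree on the second and third rows. As worded, the man in the second row may enter while receiving treatment that the concomitant-treatment section forbids during the trial.

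**Sample size, for context.** Inputs from Sample size calculation: difference 2.5, SD 6.3, two-sided alpha 0.05, power 90%, dropout 20%.

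- n per arm = 2 × (1.960 + 1.282)² × 6.3² / 2.5² = 133.5, so 134
- after dropout: 134 / 0.8 = 167.5, so 168 per arm and 336 in total, against the stated 340
- with 170 × 0.8 = 136 evaluable per arm, power = Φ(2.5 / 6.3 × √68 − 1.96) = Φ(1.312) = 0.905

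The stated figure reproduces and does not depend on the eligibility wording.

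**Hypothetical dilution, not part of the point.** If a share f of participants had no incremental response, the difference would be 2.5 × (1 − f), and power at 136 per arm would be:

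- f = 5%: difference 2.375, Φ(1.149), about 87%
- f = 10%: difference 2.25, Φ(0.985), about 84% (83.5% by the t distribution)
- f = 20%: difference 2.0, Φ(0.658), about 74%

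Both f and the zero response are assumptions.

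**The case against.** The strongest reply is that nobody would apply twelve unrelated conditions jointly. The lead-in is a slip, urologists do the screening, and the rest of the protocol shows what was meant. That stands, and it limits the practical consequence. It does not make the rule correct as written, and no other section supplies the right connective.

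It can also be said that item 3 and the concomitant-treatment section do not strictly contradict each other: one governs entry and the other conduct during the trial, so a long-term user could enrol and then have to stop. That also stands. The two can both be followed, but they fit badly, and the second does not settle what the first means.

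A reader might infer more:

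- **That the trial screens out nobody.** The inclusion criteria still require radical prostatectomy, pathologically confirmed cancer, incontinence and adequate performance status. The near-zero figure concerns the exclusion list only and comes from 'all' alone; item 3 contributes nothing to it.
- **That power falls from 90% to about 84%.** That needs an assumed 10% share, zero response in those men, and sites that really let them in. The document supports none of the three.
- **That men who know acupuncture will recognise the shallow needling and break the blind.** This is plausible for a questionnaire outcome, but the article gives no evidence for it and schedules a blinding assessment at week 6.

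**Conclusion.** The point holds as a wording error in an operative eligibility rule, with a second, independent ambiguity in item 3. Read literally, the exclusion list removes essentially nobody: below 1 in 100 million even at an assumed 20% prevalence per item under independence. The evident intent is that any single condition excludes, and sites probably act on that, so the real effect may be small and cannot be estimated from the document. Item 3 is the less easily guessed of the two, because three readings are open and they classify longer current users and recent stoppers differently. Neither defect alters the sample size of 340 or the stated 90% power. The correction should be made because these criteria carry safety and target-population functions and cost little to put right.

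**What to change.** Change 'all' to 'any' in the exclusion lead-in, and confirm that the screening forms used at the sites treat each item as sufficient on its own.

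The sponsor should state what the 6 months in item 3 means, a look-back window or a limit on the duration of current treatment, and say how men on longer current treatment and men who recently stopped are to be classified. Item 3 and the concomitant-treatment section must then be reconciled. The choice of rule is the sponsor's.

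The cost is one word in the lead-in, one reworded item, and a check of the screening forms across 20 sites. The Trial status section says that the trial is recruiting and that the protocol is at amendment 03, so the check should also cover how the criteria were applied to men already enrolled. No recalculation is needed.

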#### Withdrawal from the study

Participants will be allowed or asked to withdraw from the study in the following circumstances:
Patients who express an unwillingness to being subjected to the assigned treatment for various reasons at any stage of the trial;Patients experience an adverse event (AE) that necessitates their withdrawal from the trial;Patients who cannot fully participate in the treatment or follow-up period; andPatients can withdraw from the study voluntarily for any reason.

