^7^ECOG score: Eastern Cooperative Oncology Group score

^8^Personal history: including family history, smoking history, drinking history, drug and food allergy history, marriage history, occupational exposure history

^9^Physical examination: the researchers will conduct a comprehensive physical examination at baseline, including general appearance, skin, neck (including thyroid), eyes, ears, nose, throat, lung, heart, abdomen, back, lymph nodes, limbs, and nervous system examination. All other visits will have a brief physical examination, i.e., a general appearance examination

^10^ICIQ-UI SF: International Consultation Incontinence Questionnaire-Urinary Incontinence Short Form

^11^EPIC-26: The Expanded Prostate Cancer Index Composite 26-item version

^12^SAS: Self-Rating Anxiety Scale is a 20-item self-report assessment

^13^Major adverse event (AE) of prostate cancer (PCa): it refers to the AEs related to the progression of PCa from the time of enrollment to the end of follow-up

^14^AE: It refers to the AEs caused by the intervention measures of the project from the time of admission to the end of follow-up

^15^SAE: It refers to the serious adverse events caused by the intervention measures of the project during the period from enrollment to the end of follow-up

The trial will last 24 weeks, including treatment and follow-up periods. All participants will receive treatment for 6 weeks. Participants in both groups will receive verum or sham acupuncture three times a week (recommended interval of one day). Each acupuncture session requires approximately 20 min to perform. Sterile needles for single use (0.25 × 40 mm; Jiangsu Medical Supplies Factory Co., Ltd.) will be used in this study. Needles in the treatment group will be inserted at a depth of 0.8-1 inches and manually manipulated by rotation methods. After acupuncture, the patient's "De Qi" should be taken as the criterion (the feeling of pain and numbness). In the control group, needles will be inserted about 0.5 inch in depth and will not receive further manipulation. To prevent blind uncovering, the operator will pay attention to the depth and angle of the shallow stab. All participants will be evaluated by blind method at week 6 after acupuncture. The Blind Method Assessment is shown in Additional file 1.

All participants need to stay in the hospital for observation for at least 10 min after acupuncture, and can leave only with no discomfort.

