In order to ensure the safety of participants, in case of emergency events, it is necessary to break the blindness in advance if there is any adverse event which could not be judged whether it is related to acupuncture intervention. When the blinding is broken, the time, reason, and personnel performing the blind breaking ahead of time shall be recorded and the supervisor shall be notified in time. Once the blinding is broken, the patient would not continue to participate in the study, and the tested data should not be adopted in this study. However, the safety analysis data should still be included.

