### Adverse events

With any adverse events during treatment, protective therapeutic measures shall be taken in time to ensure the safety of participants. According to the different levels of adverse events, researchers will make the judgment if the participants will continue, suspend, or withdrawal from the study. Common treatment-related AEs including fainting during acupuncture, local bleeding, sticking of needle, subcutaneous hematoma, and itching at the sites of needle insertion. If the patient has an adverse event due to acupuncture and the investigator decided that the patient would not suitable to continue to participate the trial, the patient will be weeded out consequently.

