#### Statistical analysis

Summary tables (descriptive statistics and/or frequency tables) will be provided for all variables as appropriate. The primary outcome analysis will use the Cochran-Mantel-Haenszel (CMH) test. For continuous variables, means and standard deviations will be presented, unless the variable has a skewed distribution, in which medians, 25th and 75th percentiles will be presented. For other categorical data, between-group comparisons will be performed using a Wilcoxon rank-sum test, chi-square test, or Fisher’s exact test, as appropriate. AE incidences for each treatment group will be tested by the *χ*^2^ test or Fisher’s exact test as appropriate. All the statistical analysis will be performed using SAS version 9.4 (SAS Institute Inc) with 2-sided tests at a significance level of < 0.05. We will use the multiple imputation to handle missing data.

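### The withdrawal rules do not separate stopping treatment from leaving the study, so men who stop needling early can lose a week-6 primary outcome that could still be collected

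*Protocol article*

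**What the plan says.** The section on withdrawal from the study opens: "Participants will be allowed or asked to withdraw from the study in the following circumstances". Two of its four grounds concern adherence to treatment: "Patients who express an unwillingness to being subjected to the assigned treatment for various reasons at any stage of the trial", and "Patients who cannot fully participate in the treatment or follow-up period". The other two are an adverse event that makes withdrawal necessary, and voluntary withdrawal for any reason.

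The Adverse events section lets researchers decide whether a participant continues, suspends or withdraws. If an adverse event is due to acupuncture and the investigator judges the man unsuitable to continue in the trial, "the patient will be weeded out consequently".

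On timing, the Interventions section says "All participants will receive treatment for 6 weeks", and the Abstract defines the primary outcome as the change in ICIQ-UI-SF "score at the week 6 from the baseline". On missing outcomes, the Statistical analysis section says "We will use the multiple imputation to handle missing data" and names no missingness assumption.

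**The concern.** Voluntary withdrawal has its own item, so the two adherence grounds are more than a restatement of withdrawn consent. They make a treatment event a reason to leave the study. Nothing in the article says that outcomes are sought from a man who has stopped needling but is willing to answer questionnaires.

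This reaches the primary endpoint because treatment ends when that endpoint is measured. Incomplete treatment therefore always arises at or before the primary assessment. The loss is partly avoidable, since completing a short-form questionnaire does not depend on attending all 18 sessions.

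The loss may also be informative. Unwillingness, adverse events and incomplete treatment are plausibly linked to tolerability and perceived benefit. The arms differ in ways that could affect these: verum needling is deeper and manipulated to De Qi, sham is shallow and unmanipulated, and the acupuncturists know the allocation. If early leavers differ between arms, the estimate can drift from the effect of assignment towards the effect in men who complete treatment. An analysis plan can model missing scores, but it cannot recover scores that were never collected.

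**Working it through.** **1. The plan's sample size.** Inputs from the Sample size calculation section: difference 2.5, SD 6.3, two-sided alpha 0.05, power 90%, dropout 20%.

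- n per arm = 2 × 6.3² × (1.960 + 1.282)² / 2.5² = 133.5, so 134.
- Allowing for dropout: 134 / 0.80 = 167.5, so 168 per arm and 336 in total. The stated 340 (170 per arm) is consistent with this.
- Dropout of 20% is 34 of 170 per arm, leaving 136. Power with 136 per arm is 90.3% (noncentral t).

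The sample size is not in error. The allowance protects power; it does not protect against bias.

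**2. What is left for imputation.** In Table 1, ICIQ-UI-SF is scheduled at baseline and weeks 6, 12, 18 and 24. Between baseline and week 6 the related measures are the 72-h diary and weekly pad count at weeks 1, 2 and 4, and the 1-h pad test at week 4. A man who leaves in week 3, for example, would contribute diary and pad counts at weeks 1 and 2 only.

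**3. Bias formula.** Let w be the proportion removed in an arm and D the number of points by which removed men improve less than retained men in that arm. The arm's true mean improvement is the retained mean minus w × D. An analysis that treats removed men like retained men reports the retained mean and is too high by w × D. The error in the between-arm difference is

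bias = w(verum) × D(verum) − w(sham) × D(sham).

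This gives the diary and pad data no credit. The documents give neither w by arm nor D, so every value below is an assumption.

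| Removed, verum v sham | D, points | Bias, points |
|---|---|---|
| 20% v 20% | same in both arms | 0 |
| 20% v 10% | 2 in both | 0.10 × 2 = 0.2 |
| 20% v 10% | 4 in both | 0.10 × 4 = 0.4 |
| 15% v 25% | 2.5 in both | −0.10 × 2.5 = −0.25 |
| 20% v 20% | 5 verum, 0 sham | 0.20 × 5 = 1.0 |

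**4. Effect on the test.** With 136 per arm, SE = 6.3 × √(2/136) = 0.764. If the true effect of assignment is zero, the two-sided type I error is 1 − Φ(1.960 − bias/SE) + Φ(−1.960 − bias/SE):

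- bias 0.2: 5.8%
- bias 0.4: 8.2%
- bias 1.0: 25.8%

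Using the retained numbers that match 20% v 10% (136 and 153), SE is 0.742 and the first two become 5.8% and 8.4%.

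**5. Power.** With 170 per arm and the full 2.5-point effect, power would be 95.4%. That conflicts with step 3. If removed men improve 2 to 4 points less at 20% v 10%, the effect of assignment is 2.5 − 0.2 = 2.3 down to 2.5 − 0.4 = 2.1 points, and power with all 170 per arm is 91.9% down to 86.5%. No power gain can be claimed.

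**The case against.** The strongest reply is that the text is looser than a removal rule. The lead-in permits or requests withdrawal and does not require it. The Adverse events section offers suspension as well as withdrawal, and removes only men the investigator judges unsuitable to continue. A man who cannot take part in follow-up will supply no outcomes under any wording. All of this stands. It limits the point to the treatment half of the participation ground, to unwillingness, and to the adverse-event wording.

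A reader might infer that withdrawn men are dropped from the analysis or that their data are discarded. Neither the withdrawal section nor the Adverse events section says so, and planned imputation suggests they stay in. The only data-discarding rule concerns emergency unblinding, in the Interventions section: "the patient would not continue to participate in the study, and the tested data should not be adopted in this study". It should not be read across to the other grounds.

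A reader might also infer that imputation will treat early leavers as completers. The article does not fix that. The model and any sensitivity analyses may be in an analysis plan that is not shown, and diary and pad data can inform the model. So the bias figures illustrate assumed inputs and are not estimates. Nor does anything attribute the 20% dropout to these rules, since it may include ordinary loss to follow-up.

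Finally, the full protocol may provide for follow-up after treatment stops. That lowers confidence, but it does not change the rule as published.

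**Conclusion.** The point holds in limited form. The published rule makes unwillingness to be treated, or inability to take full part in treatment, a ground for leaving the study, and does not separate that from ending follow-up. Because treatment ends at the primary assessment and the primary scale has no interim measurement, following the rule can lose week-6 scores that could have been obtained.

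The size is unknown. It is zero with equal removal rates and equal deficits, and it can take either sign. Under the assumed 20% v 10% removal and a 2 to 4 point deficit, with no credit for auxiliary data, it is 0.2 to 0.4 points, or 8% to 16% of the 2.5-point target, with type I error of about 5.8% to 8.2%. The larger 1.0-point figure needs a 5-point deficit confined to one arm.

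That missingness is informative is a reasonable inference and not something the documents show. The case rests on estimating the effect of assignment from observed data, not on power. This should be changed; confidence is medium.

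**What to change.** In the withdrawal and Adverse events sections, define two separate events:

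- **Discontinuation of study treatment.** The man stays in the study. ICIQ-UI-SF and diary are sought at weeks 6, 12, 18 and 24, remotely if needed, and he is analysed as randomised.
- **Withdrawal from the study.** This is limited to withdrawal of consent to data collection.

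Delete inability to take full part in treatment as a ground for leaving the study, and reword the adverse-event sentence so that it refers to treatment and not to removal from the trial. When treatment stops remains with the investigator; the change concerns data collection only.

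The cost is protocol wording, some remote follow-up contacts (recruitment already uses WeChat) and possibly a line in the consent form. The Trial status section describes recruitment as under way, so the change would help only men whose outcomes had not yet been lost.
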